## Discussion

5

This study’s novelty lies not in the development of new autonomic measures, but rather in three key aspects: (1) the first application of HRT analysis in sTBI patients, providing new insights into post-ectopic beat autonomic regulation in this population; (2) the comprehensive integration of multiple autonomic measures in a large cohort of sTBI patients, allowing for robust characterization of autonomic dysfunction patterns specific to this population; and (3) the potential to establish normative values and clinical thresholds for autonomic measures in acute sTBI, which are currently lacking. This approach will provide clinicians with a more complete understanding of autonomic dysfunction in sTBI and its relationship to clinical outcomes.

Following sTBI, eAD is a complex and multifaceted issue that can significantly impact a patient’s overall health and recovery. Characterizing eAD is crucial for risk assessment, customizing pharmacological interventions, and assessing rehabilitation strategies. While small studies indicate that eAD is associated with poor outcomes following sTBI, the duration and full trajectory of eAD has been poorly characterized. This protocol outlines the data analysis procedure for quantifying acute autonomic dysfunction using cardiac telemetry waveforms. We will collect and annotate waveform data from 550 patients in a clinical trial and quantify the incidence and magnitude of eAD indices after the first day of admission. We will characterize eAD as the presence of 3 or more indices less/greater than 2.5 SDs of age/sex-standardized values measured over 24 h following admission.

In some patients, simultaneous ECG and ABP signals may be unavailable. To solve this problem, we will divide the collected data into subgroups with and without ECG information and examine eAD within both subgroups. We will report results of the planned study in one or multiple scientific papers in international peer-reviewed journals. We will note and deviations from this protocol, if any occur, in these publications.

When interpreting autonomic indices, particularly LF/HF ratio, several important caveats must be considered. The traditional interpretation of LF/HF as a simple marker of sympathovagal balance is problematic in acute TBI patients for several reasons. First, respiratory rate, which significantly influences HF power, is often mechanically controlled in these patients. Second, medications commonly used in TBI management, such as beta-blockers and vasopressors, directly affect autonomic modulation. Third, altered intracranial pressure and cerebral autoregulation can independently influence cardiovascular variability. Therefore, we recommend interpreting LF/HF alongside other autonomic measures and within the context of each patient’s clinical status, medication profile, and ventilatory parameters. This multi-parameter approach provides a more reliable assessment of autonomic dysfunction than relying on any single metric alone.

There are still some limitations in this study. Currently, this study incorporates both linear (time and frequency domain) and non-linear (PRSA) approaches to analyze autonomic function. The inclusion of PRSA as a non-linear method is particularly valuable as it can capture complex patterns of cardiovascular regulation that may be missed by traditional linear analyses. Future studies might benefit from incorporating additional non-linear methods such as entropy measures and detrended fluctuation analysis to provide an even more comprehensive assessment of autonomic dysfunction in severe TBI. Another limitation of our study is the inability to fully control for numerous confounding factors that can influence autonomic function in the critical care setting. While we account for age through stratification and statistical adjustment, several other important confounders remain uncontrolled. These include pharmacological interventions (such as vasopressors, analgesics, sedatives, beta-blockers, and anti-edema medications like mannitol), mechanical ventilation parameters, arterial CO2 levels, and timing of various therapeutic interventions. Future studies should consider implementing more complex statistical methods to better account for these factors.

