## Introduction

1

Traumatic brain injury (TBI) is a heterogeneous condition that leads to significant injury-related disability and mortality (1). TBI not only impacts the brain but also results in extracranial multi-organ dysfunction, leading to secondary brain injuries and poor clinical outcomes (2). In 2014, TBI accounted for 2.8 million Emergency Department visits, 288,000 hospitalizations, and 56,800 deaths (3). One-third of survivors of hospitalization suffer long-term disability (3). The severity of TBI falls into three severity classifications based on the Glasgow Coma Scale (GCS) score following resuscitation: mild (GCS 13–15), moderate (GCS 9–12), and severe (GCS < 9), contingent upon criteria such as the duration of loss of consciousness, post-traumatic amnesia (4). However, variation in presentation, hospital course, and outcomes within each severity category is significant. Individuals initially diagnosed with mild or moderate TBI upon hospital admission may deteriorate, necessitating escalation in TBI management (5–7).

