However, in the severe traumatic brain injury (sTBI) population, the interpretation of frequency-domain HRV metrics is complicated by several factors. Mechanical ventilation, often required for sTBI patients, can artificially alter respiratory patterns, impacting HF power and respiratory-related heart rate modulation. Additionally, the use of sedation and analgesic medications, common in sTBI management, can directly affect autonomic regulation and HRV patterns. Intracranial pressure fluctuations, characteristic of sTBI, can independently influence autonomic regulation and cardiovascular variability. Furthermore, hemodynamic management strategies involving vasopressors and fluid management can affect blood pressure variability and consequent autonomic responses. Baguley et al. investigated dysautonomia following sTBI based on the HRV analysis, finding significant differences in HRV among TBI patients, controls, and between dysautonomia and non-dysautonomia subjects (17). Froese et al. assessed the physiological relationship between pressure reactivity index (PRx) and HRV, BP, and baroreflex sensitivity (BRS) using time-series statistical methodologies in sTBI patients. They demonstrated a stronger connection between BRS, HRV, and PRx, indicating sympathetic autonomic response related to cerebrovascular reactivity derangements (18). Therefore, while these frequency-domain metrics provide valuable insights into autonomic regulation, their interpretation in sTBI patients should account for these confounding factors and be integrated with other autonomic assessment measures for a more comprehensive evaluation of autonomic dysfunction.

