### Recruitment

2.1

We will collect data from an ongoing multi-center randomized controlled trial examining the efficacy of a sTBI treatment strategy guided by both ICP and brain tissue oxygen (PbtO2) as compared to a strategy guided by ICP monitoring alone [Brain Oxygen Optimization in sTBI (BOOST), Phase 3, NCT03754114] (17). As part of the trial, the ECG waveform with four-leads and arterial blood pressure waveform data will be collected over the first 5 days of their intensive care unit (ICU) stay. Our ancillary study (AUTO-BOOST) will leverage this rich and granular waveform data to fully characterize autonomic dysfunction following sTBI.

We are sourcing data from this active clinical trial (BOOST), the trial has enrolled 550 patients. Since unexpected issues may arise during data collection, such as failures to collect data due to leads detaching or errors caused by device malfunctions, we estimate that approximately 50% of patients will have adequate cardiac telemetry data of sufficient quality for analysis. The Moberg monitor (CNS Monitor, Moberg ICU Solutions, Amber, Pennsylvania, United States) will capture and time-synchronize these analog data with other vital signs, ventilator data, and ICP/PbtO2 data, storing all data locally. A research team member will extract and upload the waveform data to a secure IBM cloud-based server. We will extract ABP, ECG data, and ventilator parameters from the Moberg device, deriving heart rate from the raw ECG tracing. We will use cleaned segments of stable recordings within 24 h of ICU admission for analysis.

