## Statistical analysis

3

The characterization of eAD requires consideration of age-specific analysis. We will stratify patients into age to account for known age-related differences in autonomic function; Within each age stratum, we will establish reference distributions based on published normative data for that specific age group; For each autonomic measure, we will use age-appropriate reference ranges from healthy controls as reported in large-scale studies. Normally, RMSSD values should fall between 19 and 75 ms (48), HRT should exhibit a turbulence onset near 0% and a turbulence slope above 2.5 ms/R-R interval (49), and BRS is around 4.87–34.07 across different age groups over 20 years old (50).

For the determination of eAD, we will quantify the incidence and magnitude of anomalies such as reduced RMSSD, HRT, and BRS, alongside increased low frequency (LF) power and an elevated LF/HF ratio, which are critical indicators. eAD will be characterized if three or more of these indicators exceed or fall below 2.5 standard deviations from age and sex-standardized values. Autonomic function measures will also be considered as continuous variables as well. For the primary analysis, we will use data from patients over their first 24 h following ICU admission to identify eAD, as well as examine the association of these measures with clinical outcomes. In exploratory analysis, we will describe autonomic function measures over the first 5 days following ICU admission.

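### The eAD–outcome association is stated to account for age only, so it cannot show that eAD carries prognostic information beyond injury severity and ICP

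*Protocol article*

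**What the plan says.** Section 3 (Statistical analysis) places two tasks in the primary analysis of the first 24 h after ICU admission: to "identify eAD, as well as examine the association of these measures with clinical outcomes". It names no outcome, model or covariate set.

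Age is handled explicitly: "We will stratify patients into age to account for known age-related differences in autonomic function". Sex appears only in the definition of the exposure: "eAD will be characterized if three or more of these indicators exceed or fall below 2.5 standard deviations from age and sex-standardized values".

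The Discussion then describes how far confounding is controlled: "While we account for age through stratification and statistical adjustment, several other important confounders remain uncontrolled". The factors it goes on to list as uncontrolled are drugs, ventilator settings, arterial CO2 and the timing of treatment. Better control is left to future studies.

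On ICP, section 1.2 says: "Intracranial pressure fluctuations, characteristic of sTBI, can independently influence autonomic regulation and cardiovascular variability", and asks that interpretation take account of such factors. Section 1.1 links refractory ICP elevation to lower heart rate variability and impaired baroreflex sensitivity. The Discussion repeats the ICP point as a caution on reading LF/HF. On severity, the Introduction grades TBI by post-resuscitation GCS and adds that "variation in presentation, hospital course, and outcomes within each severity category is significant". On data, section 2.1 says the bedside monitor will "capture and time-synchronize these analog data with other vital signs, ventilator data, and ICP/PbtO2 data".

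**The concern.** A more severe injury can plausibly depress the autonomic indices and also worsen outcome. The article supplies most of this chain. Section 1.1 says the brain injury itself sets off sympathetic activation, sections 1.1 and 1.2 say ICP acts on autonomic function, and the Introduction says prognosis differs within a GCS category. If the outcome analysis accounts for age and nothing else, an index with no prognostic content of its own can still appear associated with outcome because it marks a worse injury.

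This differs from the treatment-related confounding that the Discussion admits. It would be present even if every patient received identical drugs and ventilation.

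At stake is the meaning of the primary association. Section 1.3 wants these metrics to feed predictive models and early-warning scores. A clinician already knows the GCS and the ICP, so the useful question is whether eAD adds to them. The analysis as described does not answer it.

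**Working it through.** **Step 1. What is controlled, what is disclosed, what is on record.**

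| Factor | Said to act on autonomic indices | Adjusted for | Named as uncontrolled | Recorded |
|---|---|---|---|---|
| Age | Yes (section 3) | Yes (section 3, Discussion) | – | Needed for the strata |
| Sex | Through the standardised values | Only in defining eAD | No | Needed for the standardisation |
| Drugs, ventilation, CO2, timing | Yes | No | Yes (Discussion) | Ventilator data: yes (2.1) |
| ICP | Yes (1.1, 1.2, Discussion) | No | No; caveat only | Yes, synchronised (2.1) |
| Injury severity | Injury triggers activation (1.1) | No | No | GCS assumed on file, since it defines sTBI |

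Two links are inference rather than text: that autonomic disturbance increases with severity within sTBI, and that ICP affects outcome.

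**Step 2. Number analysable.** Section 2.1 gives 550 enrolled and about 50% with adequate telemetry: 550 × 0.5 = 275. The article states no power, outcome rate, eAD rate or effect size, so there is no figure of its own to reproduce. All confounding strengths below are assumptions.

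**Step 3. Exact illustration.** Take one binary confounder with prevalence 50%. Let eAD occur at rates e0 and e1, and poor outcome at rates y0 and y1, without and with the confounder. Within each level eAD has no effect (OR 1.0). Then:

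- P(eAD) = 0.5·e1 + 0.5·e0
- share with the confounder among eAD: c1 = 0.5·e1 / P(eAD)
- share among non-eAD: c0 = 0.5·(1 − e1) / (1 − P(eAD))
- crude outcome rates: p1 = c1·y1 + (1 − c1)·y0 and p0 = c0·y1 + (1 − c0)·y0

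Worked row (eAD 20% v 50%, outcome 30% v 60%): P(eAD) = 0.35; c1 = 0.25/0.35 = 0.714; c0 = 0.25/0.65 = 0.385; p1 = 0.514; p0 = 0.415; crude OR = (0.514/0.486)/(0.415/0.585) = 1.49.

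| eAD rate | Poor outcome | Crude OR | Chance of p < 0.05 in the expected direction, n = 275 |
|---|---|---|---|
| 30 v 40% | 40 v 50% | 1.05 | 3.7% |
| 30 v 50% | 40 v 60% | 1.18 | 10% |
| 20 v 50% | 30 v 60% | 1.49 | 35% |
| 15 v 60% | 30 v 70% | 2.18 | 88% |

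The last column counts one direction only, so the figure without confounding is 2.5%.

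**Step 4. Age-only model against a fuller model.** 1,500 simulated studies per row, n = 275, true eAD OR 1.0. Severity and ICP are correlated at 0.4, and age affects both eAD and outcome. Odds ratios in the first column are per SD of the combined severity–ICP score.

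| Score OR for eAD / outcome | Age only: OR, p < 0.05 | Age + severity + ICP: OR, p < 0.05 |
|---|---|---|
| 1.35 / 1.49 | 1.12, 6.6% | 1.00, 4.0% |
| 1.49 / 1.82 | 1.24, 12.9% | 0.99, 5.1% |
| 2.01 / 2.01 | 1.53, 34.5% | 1.00, 5.6% |
| 2.72 / 2.72 | 2.08, 79.3% | 1.01, 5.0% |

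**Step 5. Continuous index.** Section 3 also treats the measures as continuous. Model: index X = ρ·S + noise, logit P(Y) = ln(OR)·S, n = 275, outcome rate about 50%, X without effect. With X alone, ρ = 0.2 and severity OR 1.5 give about 9–10% significant. ρ = 0.3 and OR 2.0 give OR 1.22 per SD and about 33–36% significant. ρ = 0.5 and OR 2.5 give OR 1.49 and about 90%. At ρ = 0.1 and OR 1.5 there is little or no inflation. With S itself in the model the rate returns to about 5%.

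**Step 6. GCS as a proxy.** Steps 4 and 5 adjust for severity measured without error. If the covariate correlates only 0.4–0.6 with true severity (assumed), about 18–26% remain significant in the ρ = 0.3, OR 2.0 case, and about 60–79% in the ρ = 0.5, OR 2.5 case. The unadjusted rates were about 33–36% and 90%.

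**The case against.** The strongest reply is that the article never sets out the outcome model. A condensed article may leave covariates to a fuller document, and the limitation in the Discussion concerns influences on autonomic function, not terms in an outcome regression. This stands in part: an age-only outcome model is what a reader might infer, not something section 3 writes down. But the Discussion does say what is accounted for and that other confounders are not, so this is a stated position rather than silence.

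Second, ICP is not ignored. A reader might infer from its absence among the uncontrolled factors that it was overlooked. The article names ICP as an influence in three places, and its list of uncontrolled factors is introduced as examples. What remains is that a caveat on interpretation is not an adjustment, and injury severity receives not even a caveat.

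Third, a reader might infer that confounding defeats the early-warning purpose in section 1.3. It does not. A marker of worse injury can still predict deterioration, and prediction needs no independent effect. Only a claim of independent or incremental value is unsupported.

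Fourth, the cohort is restricted to sTBI, which narrows the GCS range, and under weak confounding the bias is negligible. Both points are right. GCS is also an imperfect proxy, and ICP in the same 24 h is managed under the trial strategy and may lie on the pathway from injury to outcome. These limit what adjustment can achieve; they do not favour leaving it out.

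**Conclusion.** The concern holds in limited form. As described, the primary association cannot show that eAD carries prognostic information independent of, or beyond, injury severity. It can still show an association and may still predict outcome.

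The probable direction of the bias, making eAD look more prognostic than it is, follows from the article's own account of injury and ICP together with the two inferred links in step 1. The size does not follow from the article. With about 275 patients and no true effect, the false-positive rate for an independent effect is about 5–10% under weak confounding and about 80–90% under strong confounding, all on assumed strengths. Adjusting for GCS and early ICP should reduce the bias. Because GCS is only a proxy, it cannot be expected to remove it.

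**What to change.** In section 3, state that the eAD–outcome and index–outcome models include age and baseline post-resuscitation GCS. GCS is assumed to be on file because it defines sTBI.

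Report a second model that adds an early ICP summary from the synchronised record, such as the mean over the first 24 h. Label it as possibly adjusting for a factor on the pathway, and show both models side by side.

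In the Discussion, name residual injury severity and ICP as incompletely controlled. Confine the conclusions to association or prediction unless the adjusted models support more.

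The cost is one or two degrees of freedom, a little more analysis and some wording. ICP needs no new data collection.

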## Appendix

RMSSD is calculated between inter-beat intervals of sinus beats using the following formula:

(1)
$$\mathrm{RMSSD}=\sqrt{\frac{1}{N-1}\left(\overset{N-1}{\underset{i=1}{\sum }}{\left(RR_{i+1}-RR_{i}\right)}^{2}\right)}$$

Sensitivity measures the proportion of true PVCs correctly identified by the algorithm, calculated as follows:

(2)
$$Sen=\frac{TP}{TP+FN}$$

where TP stands for true positives and FN indicates false negatives.

Specificity quantifies the proportion of non-PVCs correctly identified, computed as follows:

(3)
$$\mathrm{Spec}=\frac{TN}{TN+FP}$$

where TN stands for true negative; FP stands for false positives.

Accuracy represents the overall correctness of PVC detection, determined as following formula:

(4)
$$Acc=\frac{TP+TN}{N}$$

where N is the total number of instances.

F1-score provides a balanced measure of the algorithm’s precision and recall, computed as follows:

(5)
$$F1=\frac{2*\left(\mathrm{precision}*\mathrm{recall}\right)}{\left(\mathrm{precision}+\mathrm{recall}\right)}$$

where precision is the ratio of TP to the sum of TP and FP, and recall is the same as sensitivity.
